#### Visit 2: confirmatory laboratory results and treatment plan

If the confirmatory laboratory HCV RNA result is negative, the study nurse/doctor will contact the participant (via phone call immediately) and the participant will be asked to stop treatment immediately and to return unused DAAs either directly to the clinic or an outreach worker, or in some cases via a prepaid envelope provided to them in advance. This group of participants will be actively followed up for a face-to-face appointment to ensure they understand the test result and implications and to collect information on their experience of treatment. However, following this next visit, the participant will exit the study. Standard harm reduction messaging and window periods for detection of HCV will be discussed with the participant.If the confirmatory laboratory HCV RNA result is positive, the participant will be assessed for eligibility for treatment continuation based on other laboratory investigations. If a participant is eligible, the participant will continue treatment for a total of 12 weeks.

Participants returning laboratory investigations indicating renal dysfunction, with abnormally high levels of serum creatinine where eGFR <30, will be asked to pause treatment while they seek specialist review and advice on whether to continue treatment.

Participants returning laboratory investigations indicating cirrhosis (FIB-4 score >3.25; ALT or AST >200 U/L; bilirubin >1.14 mg/dL; albumin <3.5 g/dL without other obvious cause) will be discussed with supervising specialist for a decision regarding pausing treatment or organising a specialist referral for review without pausing treatment.

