### Study exit

Participants may exit the study at various time points: when they choose to withdraw from the study, when the clinician identifies a medical issue/ineligibility prompting participant withdrawal or when they have been identified as lost to follow-up due to no longer being contactable.

Throughout, there will be a minimum of three attempts over up to 3 weeks to contact participants to arrange the follow-up appointment if the participant misses the scheduled appointment. In the case of SVR, participants will remain in the study until the SVR20 time point passes; they will be contacted up to four times, every 4 weeks to attempt to arrange for SVR appointment.

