No physical signs of decompensated cirrhosis.No comorbid conditions that require further investigation or referral to a specialist.No contraindicated medications (amber/red using online Liverpool Drug Interaction Checker).

If the participant is deemed eligible for treatment, the study doctor will provide 28 days of SOF/VEL and the participant will be asked to begin treatment. The blood sample for confirmatory RNA testing must be collected prior to providing any treatment medication. If there is an issue with the blood sample itself, the participant will be asked to return to the study site as soon as possible for a follow-up blood draw. Only after confirmatory RNA laboratory results will a second bottle of 28 SOF/VEL doses be provided for the participant to continue their treatment course.

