##### Proportion ‘overtreated’ for hepatitis C

The proportion of participants ‘overtreated’/‘unnecessarily treated’ for hepatitis C in the same-day treatment model (those who are HCV antibody positive at 5 min but RNA negative), where participants were prescribed hepatitis C treatment or initiated hepatitis C treatment and later received a hepatitis C RNA negative test result will be calculated. The proportion of this group experiencing adverse events will also be described.

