### Adverse events and reporting

This study uses a drug with side effects that are already known.^49^ However, the study will trial a modified clinical pathway outside of current guidelines for HCV treatment in arm 2, that is, starting participants onto treatment drug without confirmation of HCV RNA status (current HCV infection) and without receipt of liver function and platelets investigation results to complete cirrhosis assessment.

It will therefore report adverse events that, in the opinion of the investigator, are not deemed to be expected or are increased in severity from prior observations. Adverse events considered related to the study drug administration will be captured up to 24 weeks after the last recorded study drug dose.

Burnet Institute, with Médecins du Monde as the study sponsor, is responsible for reporting adverse events and protocol modifications to Data Safety Monitoring Board and to the relevant Ethics Committees, where appropriate.

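### The 24-week window for drug-related adverse events is longer than the follow-up described, above all for overtreated arm 2 participants, who exit after their next visit

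*Protocol article*

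**What the plan says.** Four parts of the Protocol article bear on this.

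- **Adverse events and reporting.** "Adverse events considered related to the study drug administration will be captured up to 24 weeks after the last recorded study drug dose". The sentence makes no exception for participants found to be RNA negative. The same section limits reporting to events that, in the investigator's opinion, "are not deemed to be expected or are increased in severity from prior observations".
- **Arm 2, Visits 1 and 2.** At Visit 1, for those eligible, "the study doctor will provide 28 days of SOF/VEL and the participant will be asked to begin treatment". If the RNA result is then negative, the participant is phoned, asked to stop, and actively followed up for a face-to-face appointment, partly "to collect information on their experience of treatment". Then: "However, following this next visit, the participant will exit the study".
- **Proportion 'overtreated' for hepatitis C.** After defining the overtreated proportion, the section adds: "The proportion of this group experiencing adverse events will also be described". It gives no time window.
- **Study exit and Project timeline.** For the SVR assessment, "participants will remain in the study until the SVR20 time point passes". Enrolment closes by June 2026 at the latest, the study closes in December 2026, and minimum follow-up is given as 6 months.

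**The concern.** The article states a specific observation window for drug-related harm, and its own visit schedule does not supply that window. The shortfall is largest for people who took the drug without current infection. They cannot benefit from treatment, and they are followed for the shortest time.

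This group is central to the safety case for arm 2. The Background accepts that uninfected people may experience side effects of treatment. The adverse event section introduces its reporting by noting that arm 2 departs from current guidelines. A reader who meets the adverse event proportion for overtreated participants would naturally attach the only window the article gives, 24 weeks. If the data stop at the exit visit, later events have no described route into that figure, and a low proportion would look more reassuring than it is.

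**Working it through.** The article gives no figure to reproduce here. The check compares the stated window with the described contact, then sizes the group.

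**Step 1. Overtreated participants.** They hold at most 28 days of drug before the RNA result, so the last dose falls between week 0 and week 4 from Visit 1.

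- Window closes at: week of last dose + 24.
- Earliest: 0 + 24 = week 24. Latest: 4 + 24 = week 28.
- Last described contact: the face-to-face appointment after the RNA result. It has no stated date.

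Nothing is scheduled between that appointment and weeks 24 to 28. The other contacts do not fill the gap. Visit 3, where side effects and adverse events are documented, comes only once treatment continues. The arm 1 follow-up that arm 2 then adopts applies to confirmed infection, and RNA-negative participants exit in arm 1 as well.

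**Step 2. Treated RNA-positive participants.**

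- Window closes 24 weeks after treatment; retention ends at 20 weeks. Gap: 24 − 20 = 4 weeks.
- From treatment start: 12 + 24 = 36 weeks.
- Minimum follow-up: 6 months, about 26 weeks. Shortfall for a last enrolee: 36 − 26 = 10 weeks.
- Even counting from 1 June to 31 December 2026, there are 213 days, or 213/7 = 30.4 weeks, still short of 36.

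These dates come from Project timeline. The Abstract has recruitment itself closing by December 2026, which would leave less time.

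**Step 3. Size of the overtreated group.** Inputs from Table 3: arm 2 targets of 115 (Armenia), 120 (Georgia) and 115 (Tanzania), with RNA prevalence *p* of 75%, 30% and 75%. I read *p* as the proportion among antibody positives. Georgia supports this: 0.58 × 0.30 = 17.4%, close to the 18% viraemic prevalence given in the study setting. I assume that every antibody-positive participant reacts by 5 min and starts treatment.

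| Country | Target counts all starts: target × (1 − p) | Target counts RNA-positive starts: target × (1 − p)/p |
|---|---|---|
| Armenia | 115 × 0.25 = 28.75 | 115 × 0.25/0.75 = 38.3 |
| Georgia | 120 × 0.70 = 84 | 120 × 0.70/0.30 = 280 |
| Tanzania | 115 × 0.25 = 28.75 | 115 × 0.25/0.75 = 38.3 |
| Total | 141.5, about 142 | 356.7, about 357 |

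The article does not settle which count applies. The column heading in Table 3 refers simply to treatment initiation, while the uptake outcome is defined among RNA-positive participants.

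**The case against.** The strongest reply is that the 24 weeks is an outer limit for accepting reports, not a promise of scheduled contact. Spontaneous reports after exit would fit that wording. The case report form details, the consent form and the safety board's terms of reference sit in supplements or ethics files that are not shown, and the full protocol may describe a route. This stands in part: passive reporting is possible. But the article says that events will be captured, describes participants as having exited, and names no route afterwards. That is a mismatch between two statements in the document, not merely omitted detail.

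Some stronger readings are tempting, and the document does not support them.

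- *A reader might infer that the adverse event outcome in overtreated participants cannot be delivered.* It can. It is a descriptive proportion with no stated window, and the exit appointment is actively pursued and collects treatment experience. It can be reported up to that visit for those who are reached.
- *A reader might infer a biased comparison between arms or with treated participants.* No such comparison is planned for this outcome, and overtreatment is defined only in arm 2.
- *A reader might infer that a safety board end point is compromised.* The named end point is the proportion over-treated, which is known once treatment start and the RNA result are recorded. Early exit does not change it. Serious adverse events are also named, but for the trial as a whole.
- *A reader might want the share of the 24 weeks that is observed.* The exit visit has no stated date, so the document supports no such percentage.

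**Conclusion.** The point holds as an inconsistency. The capture window of 24 weeks after the last dose is not matched by the follow-up described for overtreated participants (exit after the next visit), for treated participants (retention to 20 weeks), or for late enrolees (36 weeks needed against a minimum of about 26). The adverse event proportion in overtreated participants remains reportable, but only for the period up to the exit visit.

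The group concerned is at most about 142 or about 357 people, depending on how the target of 350 is counted. Both figures are conditional on the Table 3 prevalences and on all antibody-positive participants reacting by 5 min and starting. In practice some will react only after 5 min and receive no same-day treatment. In the pooled cohorts cited in the Background, none of those late reactors was RNA positive, so this rule removes RNA-negative people in particular and lowers both figures.

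No primary outcome, sample size or planned test is affected. The correction is still worth making because it concerns safety information on people who cannot benefit from the treatment, and it is cheap.

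**What to change.** Reconcile the arm 2 Visit 2 procedures, the overtreated outcome, Adverse events and reporting, and Project timeline, so that they give one adverse event window for each group. Either of two routes would do.

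1. **Keep the 24 weeks.** State that overtreated participants remain open to adverse event reports until the window ends, by passive reporting plus one call. State also how the last weeks are covered for treated participants and for late enrolees. The cost is one extra contact per overtreated participant, at most about 142 or 357 calls, and a timeline that accommodates the window.
2. **Restate the window.** Change the adverse event section to match the follow-up that will actually occur in each group, and label the overtreated outcome *adverse events up to the exit visit*. The cost is wording only. The price is that later events in this group are not sought.

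Under either route, report the observation time behind the proportion and the number of overtreated participants who did not attend the exit appointment. No change to treatment or to any stopping rule is involved.

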#### Treatment monitoring, dispensing and outcome assessment

Once HCV RNA status is confirmed, follow-up will continue as per arm 1 study procedures.

### Study outcomes

The three primary research questions and outcomes are:

Does the same-day treatment initiation model (arm 2) increase hepatitis C treatment uptake and achievement of SVR (cure) among people who inject drugs compared with the simplified care model (arm 1)?What is the feasibility of implementing a decentralised hepatitis C simplified care model (arm 1) and the same-day treatment care model (arm 2) in the varied healthcare settings in the three study countries (Armenia, Georgia and Tanzania)?What is the comparative cost-effectiveness between the same-day treatment initiation model (arm 2) and the simplified care model (arm 1)?

The secondary research questions and outcomes pertain to the acceptability of the two care models to participants, to healthcare practitioners including the barriers and enablers to support scale-up of these models in country. Additional secondary outcomes include:

the time to treatment initiation and the proportion completing treatment;the test performance (sensitivity, specificity, positive predictive values and negative predictive values) of the 5 min read-time OraQuick HCV antibody result in identifying participants with viraemia from those without viraemia;the optimal ‘cut-off’ read-time to identify participants with viraemia (using arm 1 and arm 2 data) to reduce the proportion of participants without viraemia who are ‘overtreated’ for hepatitis C in the same-day treatment initiation model of care;comparison of the care cascade for both arms 1 and 2 with available historical data, where feasible, including the proportion of people who inject drugs reached through the models.

### Participant timeline

Online supplemental material 5 displays the participant timeline.

### Sample size

The primary study aim (aim 1) is to assess if same-day treatment initiation model (arm 2) increases hepatitis C treatment uptake and achievement of SVR, compared with a simplified care model (arm 1). The study is powered to measure the primary outcomes of treatment uptake and cure in arm 1 and arm 2 in a pooled analysis of all three countries. In addition, we will compare retention in care between arm 1 and arm 2, in each country individually. The sample size is presented below (table 3).

**Table 3 T3:** Country and site enrolment and treatment targets

Country	Site	Target enrolment	Target DAA initiation arm 1	Target DAA initiation arm 2
Armenia	Yerevan, National Center for Infectious Diseases	500	58	58
	Shirak, Gyumri Medical Center	164	19	19
	Lori, Vanadzor Medical Center	163	19	19
	Syunik, Kapan Medical Center	163	19	19
	**Total (Armenia**)	**990**	**115**	**115**
Georgia	Tbilisi, Hepa plus	1100	18	18
	Rustavi, New Vector	360	12	12
	Gori, Step to Future	440	42	42
	Xenon	1200	48	48
	**Total (Georgia**)	**3100**	**120**	**120**
Tanzania	Dar es Salaam, Mukikute	522	60	60
	Dar es Salaam, Temeke Regional Referral Hospital MAT Clinic	478	55	55
	**Total (Tanzania**)	**1000**	**115**	**115**
**Total**		**5090**	**350**	**350**

* Sample sizes based on the following antibody and RNA prevalence estimates: Armenia: 39% HCV Ab prevalence, 75% HCV RNA prevalence. Georgia: 58% HCV Ab prevalence, 30% HCV RNA prevalence. Tanzania: 40% HCV Ab prevalence, 75% HCV RNA prevalence.

Ab, antibody; DAA, direct-acting antiviral; HCV, hepatitis C virus.

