#### Superiority of ‘same-day initiation’ (arm 2) versus ‘simplified care pathway’ (arm 1)

Acknowledging there are considerable uncertainties around expected uptake of DAAs in both arms, we examined the required sample size in various scenarios of treatment uptake where the intervention (arm 2) would be 5%–10% superior to the simplified care (arm 1). A sample of 700 (350 in each arm) would enable a minimum effect size of 7% favouring arm 2 (presuming 85% uptake in arm 1 simplified care arm) to be detected with 80% power at the 5% significance level. We have assumed 85% treatment initiation based on previous studies that have implemented simplified care pathways in LMIC settings,^17^ accounting for a 15% loss to follow-up prior to treatment initiation. We expect cure rates to be equal across both arms (~95%).

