#### Assessing outcome 1: impact of same-day treatment initiation model on treatment uptake and cure (arm 2 vs arm 1)

The proportion of participants initiating hepatitis C treatment and cured in the simplified care model (arm 1) compared with the same-day treatment care model (arm 2) will be calculated.

The outcome of treatment uptake will be a binary outcome measured by the proportion of participants who are RNA positive and are prescribed treatment and who self-report initiating treatment. The outcome of cure will be measured by the proportion who achieve SRV among those prescribed treatment. Analyses will be conducted using a per-protocol basis, with patients analysed according to the appropriate treatment allocation and study arm following eligibility and exclusion study criteria. Those who are enrolled in arm 2 and later treated via arm 1 study procedures are excluded from primary analyses.

All available binary outcomes will be analysed at the patient level using mixed-effects logistic regression models with random intercepts for clinic and fixed effects for interventions. Models will adjust for covariates, based on any differences in participant characteristics between arm 1 and arm 2 at baseline. These covariates may include: opioid substitution therapy status, injecting frequency, history of incarceration and housing status. ORs and 95% CIs will be reported.

Where data are available, treatment uptake and cure outcomes from arms 1 and 2 will also be compared with available historical data specific to each study country (Armenia, Georgia and Tanzania) and/or globally.

Primary research question #2: What is the feasibility of implementing a decentralised hepatitis C simplified care model (arm 1) and the same-day treatment care model (arm 2) in the varied healthcare settings in the three study countries (Armenia, Georgia and Tanzania)?

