#### Assessing secondary outcomes

##### Impact of same-day treatment initiation model on treatment completion and cure

Participants will be classified as completing treatment if they self-report that they have taken at least 8 weeks of treatment, with <14 days missed doses. Proportion completing treatment will be assessed among those who were confirmed RNA positive. The proportion of participants who complete hepatitis C treatment will be compared between arms. We will also assess treatment completion based on completion of the full 12-week treatment course.

The proportion of participants who achieve SVR (4–20 weeks post-treatment completion) among those who were confirmed RNA positive and initiated hepatitis C treatment in the simplified care model (arm 1) will be compared with the same-day treatment care model (arm 2), using per-protocol analysis of those allocated to each arm.

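### The protocol claims power for both uptake and cure, but its only superiority calculation is for uptake, and it expects no difference in cure

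*Protocol article*

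**What the plan says.** *Sample size* states aim 1 as whether arm 2 "increases hepatitis C treatment uptake and achievement of SVR, compared with a simplified care model (arm 1"). It then says: "The study is powered to measure the primary outcomes of treatment uptake and cure in arm 1 and arm 2 in a pooled analysis" across the three countries.

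The superiority subsection carries the only calculation behind that statement: "A sample of 700 (350 in each arm) would enable a minimum effect size of 7% favouring arm 2". Arm 1 uptake is taken to be 85%, and the figures stated are 80% power at the 5% level. The paragraph closes: "We expect cure rates to be equal across both arms (~95" per cent). The equivalence subsection sets its 10% level for a range of uptake values. Neither subsection gives a power or precision figure for cure.

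*Assessing outcome 1* treats both as primary: it compares the arms on the proportions who start treatment and who are cured. Cure is measured there among those prescribed treatment, and all binary outcomes get the same mixed-effects logistic model with odds ratios and 95% confidence intervals. *Assessing secondary outcomes* then has a subsection headed "Impact of same-day treatment initiation model on treatment completion and cure", which compares SVR between arms again, this time among participants confirmed RNA positive who initiated treatment. The list of additional secondary outcomes under *Study outcomes* does not include SVR.

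**The concern.** The power statement covers two outcomes, but the calculation supports one. For the other, the protocol asks whether arm 2 increases it while expecting no increase. No sample size can give high power to detect a difference that is assumed to be zero, so for cure the statement describes a property the design does not have.

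This matters because the result the protocol expects is higher uptake with similar cure. A reader who takes aim 1 and the power statement at face value could treat a non-significant cure comparison as a well-powered negative finding, or as a failure to meet an aim that names both outcomes. The double listing adds to this, since it is unclear which cure comparison is primary. The two denominators need not coincide: in arm 2 treatment is prescribed before the RNA result is known, and a prescription does not guarantee a start.

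**Working it through.** **Inputs.** All come from the superiority subsection unless noted: 350 per arm; uptake 85% in arm 1 and 92% in arm 2 (85% plus 7 points); cure 95% in both arms; 5% level. Sidedness is not stated; I take two-sided. Clinic clustering and covariate adjustment are ignored.

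**1. Reproduce the stated size for uptake.** Pooled-variance z-test:

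- Mean proportion = (0.85 + 0.92)/2 = 0.885.
- SE under the null = √(2 × 0.885 × 0.115/350) = 0.02412.
- SE under the alternative = √((0.85 × 0.15 + 0.92 × 0.08)/350) = 0.02397.
- Power = Φ((0.07 − 1.96 × 0.02412)/0.02397) = Φ(0.949) = 82.9%.
- For 80% power the formula needs 325 per arm, or 353 with continuity correction. One-sided 5% would need 256.

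So 350 per arm is reproduced for uptake at two-sided 5%.

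**2. Power for a cure difference on the same sample.** Cure is assessed in people who start. Expected starters are 350 × 0.85 = 297.5 (about 298) and 350 × 0.92 = 322. The same formula with unequal groups gives:

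| Cure, arm 1 vs arm 2 | SE null | SE alternative | Power |
|---|---|---|---|
| 95% vs 97% | 0.01568 | 0.01580 | 25% |
| 95% vs 98% | 0.01465 | 0.01484 | 53% |
| 95% vs 99% | 0.01354 | 0.01379 | 84% |

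For example, for 95% vs 97%: Φ((0.02 − 1.96 × 0.01568)/0.01580) = Φ(−0.679) = 25%. Power passes 80% only when arm 2 cure is close to 99%. At the assumed equality, the chance of a significant result favouring arm 2 is 2.5%.

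**3. Literal reading of aim 1 (both outcomes increase).** With cure counted among starters, the two tests are nearly independent. Joint power = 0.829 × 0.025 = 2.1%. A simulation of 400,000 trials, drawing uptake and then cure among starters, also gives 2.1%.

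**4. Dependence on the denominator.** If cure were counted among all RNA-positive participants, the proportions would be 0.85 × 0.95 = 80.75% and 0.92 × 0.95 = 87.4%. Power for cure alone would be 67%, and simulated power for both outcomes about 66%. That is not the definition in *Assessing outcome 1*.

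**5. Dependence on what 350 counts.** Table 3 uses 350 as the number starting treatment. The RNA-positive denominators would then be about 350/0.85 = 412 and 350/0.92 = 380. Uptake power rises to 87%, and both-outcomes power is 0.870 × 0.025 = 2.2%.

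**6. What the sample can do for cure.** The 95% confidence interval half-width for the difference at 95% cure is 1.96 × √(0.95 × 0.05 × (1/298 + 1/322)) = 0.034, or 3.4 points.

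**The case against.** The strongest reply is that being powered to measure cure may mean estimating it. Step 6 shows that the sample does this well: a half-width of 3.4 points is useful, and if the 10% equivalence level were applied to cure (the protocol applies it to uptake), power would exceed 99%. That stands, and it shapes the fix. It does not rescue the sentence, because the aim it serves says that arm 2 increases both outcomes and no precision target is given.

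A second reply is that the comparison of SVR under secondary outcomes may be a supporting analysis. That is possible, but the text does not say so, and it changes the denominator without comment.

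Three stronger readings are tempting and are not supported:

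- A reader might infer that two primary outcomes without a hierarchy or alpha split nearly double the false-positive rate. *Dissemination* promises a full statistical analysis plan, which is not shown and may settle this. The protocol also states no rule under which either outcome alone would suffice.
- A reader might infer that the trial is bound to fail because both outcomes must be significant. No such rule is stated either. The 2% shows only what the literal wording of the aim would imply.
- A reader might infer that a null result on cure would trigger the equivalence fallback. That subsection frames the fallback by uptake.

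**Conclusion.** The contradiction is in the document and does not depend on the unseen analysis plan. *Sample size* claims power for uptake and cure; the superiority subsection supports uptake only (82.9% at two-sided 5%) and assumes that cure is equal. For cure differences of 2 and 3 points in arm 2's favour, power is about 25% and 53%. Power to show an increase in both is about 2% when cure is counted among those treated, and about 66% on a denominator that the protocol does not use. Cure is also analysed under two headings with two denominators.

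These figures assume two-sided 5% tests, the protocol's uptake and cure rates, and starters as the stand-in for those prescribed treatment. The sample size itself is sound for uptake, so this should be corrected but does not threaten the design.

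**What to change.** - In *Sample size*, limit the power statement to treatment uptake.
- In *Study outcomes*, *Sample size* and *Assessing outcome 1*, name uptake (arm 2 versus arm 1, pooled over countries, two-sided 5%) as the contrast that decides the superiority claim in aim 1.
- Report cure as an estimated difference with a 95% confidence interval, and state the expected half-width of about 3.4 points.
- Give cure one classification and one denominator, the same in *Assessing outcome 1* and *Assessing secondary outcomes*.
- If a formal claim on cure is wanted, test it only after uptake is significant.

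The cost is wording in the protocol and the matching lines of the analysis plan, settled before the arms are compared. No participants or data are added. The downside is that cure can no longer carry a stand-alone superiority claim, which the protocol does not expect to make.
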